## **3 Cohorts, inclusion criteria, and analytic sets**

Primary derivation set (APOL1-HR, preserved eGFR):

Inclusion: APOL1 genotype = high-risk (two risk alleles: G1/G1, G2/G2, G1/G2), available plasma proteomics (SomaScan platform), baseline eGFR > 60 mL/min/1.73 m^2 measured at or 2 months before or 1 month after of sampling, available UACR (or imputed as specified).

Final sample size in derivation set:  $N = 851$ . Baseline descriptive statistics, event counts, and follow-up summaries are provided in manuscript. Key cohort summary (derivation APOL1-HR preserved-eGFR): mean age 49.2 years; female proportion 66.5%; mean eGFR 90.6 mL/min/1.73 m^2; median UACR 17.23 mg/g; composite event rate 17.98% ( $n = 153$ ); mean time to event 6.51 years; median follow-up 7.3 years.

Secondary analytic sets:

APOL1-HR with existing CKD at baseline: 262 participants included for comparison and benchmarking of APRS behavior in established disease.

APOL1-low-risk extension: an additional 995 participants to evaluate specificity and cross-genotype performance.

EUR comparison set (review-only):  $N = 514$  (used for method comparisons but not central to the APOL1-focused primary aims).

External validation cohorts

ARIC (Atherosclerosis Risk in Communities): African-ancestry subset with SomaScan proteomics (where available).

UK Biobank (UKB): African-ancestry subset with Olink proteomics (smaller targeted panels). Because platforms differ, apply the prespecified cross-platform mapping and multi-output imputation.

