#### 3.2 Penn Medicine BioBank (Primary Cohort)

PMBB is an EHR-linked biobank at the University of Pennsylvania with >40,000 participants, ~30% non-European ancestry. We will identify all African-American PMBB participants with APOL1 high-risk genotype (two risk alleles: G1/G1, G2/G2, or G1/G2), age ≥18, and baseline eGFR >60 mL/min/1.73m^2. APOL1 genotype was determined via whole-exome sequencing (Regeneron) or equivalent genotyping. Plasma proteomic profiles (7,549 proteins) were measured at baseline using the SomaScan aptamer platform. We have identified 1,113 eligible participants for the primary cohort (expanded from 550 in the prior dataset). Additional CKD participants with APOL1 high-risk genotype and 967 African ancestry APOL1 low-risk participants (267 newly added) and 698 European ancestry APOL1 low-risk were included as external reference. Baseline covariates include age, sex, eGFR (CKD-EPI 2021), and albumin-to-creatinine ratio (UACR). To better enable comparison between the African ancestry APOL1 high-risk and low-risk groups, propensity score matching was applied using age, sex, eGFR, UACR, diabetes, hypertension, and cardiovascular disease, with separate matching performed for participants with eGFR >60 and ≤60 mL/min/1.73 m^2 (Appendix 1 to 3).

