### **3.7 Statistical Analysis**

The APOL1–high-risk cohort will be randomly divided into an 80% training set and 20% test set (stratified by outcome incidence). In the training set, candidate proteins will be selected via an elastic-net penalized Cox proportional hazards regression (age, sex, baseline eGFR, and log2(UACR) included as unpenalized covariates). Tuning parameters ( $\alpha$ ,  $\lambda$ ) will be chosen by 8-fold cross-validation. The final APRS model will include the nine selected proteins plus the four clinical covariates. Model discrimination will be quantified

by time-dependent AUC (tAUC) at prespecified time points and Harrell's C-index. Model performance will be compared to the KFRE (4-variable equation) and established CKD risk scores.

Proportional hazards assumptions for APRS and covariates will be tested using Schoenfeld residuals. Sensitivity analyses will address potential biases: we will apply inverse-probability-of-censoring weighting (IPCW) to account for informative loss-to-follow-up, computing weights within the training set. Feature stability will be assessed via bootstrap resampling. We will compute net benefit using decision-curve analysis (assuming equal weight for false positives and negatives). To gauge clinical utility, we will calculate the number needed to treat (NNT) to prevent one composite event under a hypothetical APOL1-targeted therapy: assuming a relative risk reduction of 27% (as reported for inaxaplin), NNT will be derived as the reciprocal of the absolute risk reduction. Comparisons of NNT between APRS-based risk stratification and standard models (KFRE) will be reported. All tests will be two-sided with  $\alpha=0.05$ .

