**Appendix 1 Propensity score matching for APOL1 high-risk and APOL1 low-risk with eGFR>60 cohort**

|                                              | APOL1 high-risk | APOL1 low-risk |         |                           |         |
|----------------------------------------------|-----------------|----------------|---------|---------------------------|---------|
|                                              |                 | Initial cohort |         | Propensity score matching |         |
| Number                                       | 851             | 944            | P value | 874                       | P value |
| Age - yr                                     | 49.22±15.07     | 50.37±13.81    | 0.09    | 49.9±14.03                | 0.33    |
| Female - no. (%)                             | 566(66.51%)     | 610(64.62%)    | 0.4     | 568(64.99%)               | 0.51    |
| SBP - mmHg                                   | 128.54±17.79    | 129.34±17.46   | 0.34    | 129.3±17.41               | 0.37    |
| DBP- mmHg                                    | 77.59±11.9      | 77.51±11.44    | 0.88    | 77.42±11.47               | 0.76    |
| Body Mass Index - kg/m           | 32.27±7.84      | 32.06±7.82     | 0.57    | 32.29±7.83                | 0.95    |
| Hemoglobin A1c (%)                           | 6.57±1.81       | 6.36±1.36      | 0.11    | 6.39±1.39                 | 0.19    |
| Creatinine (mg/dL)                           | 0.88±0.21       | 0.84±0.19      | <0.01   | 0.86±0.18                 | 0.07    |
| Blood Urea Nitrogen (mg/dL)                  | 13.04±4.98      | 12.44±4.34     | <0.01   | 12.56±4.39                | 0.03    |
| eGFR - ml/min/1.73m              | 90.59±17.04     | 93.04±16.38    | <0.01   | 91.96±16.39               | 0.09    |
| UACR (IQR) - mg/g                            | 17.23(11-31)    | 15.31(12-24)   | 0.02    | 15.31(12-24)              | 0.05    |
| 30~299 - no. (%)                             | 112(13.16)      | 153(16.21)     |         | 138(15.79)                |         |
| ≥ 300 - no. (%)                              | 25(2.93)        | 24(2.54)       |         | 23(2.63)                  |         |
| Red Blood Cells (×10  /μL)       | 4.32±0.63       | 4.35±0.61      | 0.43    | 4.34±0.61                 | 0.44    |
| White Blood Cells (×10  /μL)     | 7.36±3.46       | 7.21±3.08      | 0.32    | 7.21±3.12                 | 0.33    |

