### **6.4 Feature Selection and modeling**

#### **6.4.1 Training and Testing Set**

The datasets will be partitioned into a training set comprising 80% of APOL1-HR PMBB participants and a testing set comprising 20%. To maintain balance between the training and validation sets, we stratify based on key clinical parameters, which will be detailed in the Table of the main text.

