### **6.4.3 Final modeling:**

After the iterative sampling and model fitting process, the best-performing model was identified based on the lowest cross-validated partial likelihood deviance within the testing set. The final set of selected proteins and their corresponding coefficients were then used to construct the prognostic model. This finalized model was refitted on the entire training dataset to derive the final coefficients, which were subsequently applied to generate the APOL1 Proteomic Risk Score (APRS) with the clinical confounders for downstream validation and external cohort analyses.

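### Nothing in the plan confines the high-risk side of the cross-genotype APRS comparison to unseen participants, so part of any high-risk minus low-risk gap in discrimination could be optimism

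*Combined protocol and SAP*

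**What the plan says.** - **Purpose.** SAP 3 lists, as a secondary set, "APOL1-low-risk extension: an additional 995 participants to evaluate specificity and cross-genotype performance". A second secondary set is the high-risk group with CKD: "262 participants included for comparison and benchmarking of APRS behavior in established disease".
- **Derivation set.** SAP 3 gives "Final sample size in derivation set" as 851 (153 composite events). Protocol 3.7 has the high-risk cohort "randomly divided into an 80% training set and 20% test set", and SAP 6.4.1 repeats the 80/20 split. Supplementary Table 1 shows 680 training and 171 testing participants.
- **Comparison frame.** Protocol 3.2: "To better enable comparison between the African ancestry APOL1 high-risk and low-risk groups, propensity score matching was applied". The table for preserved kidney function is Appendix 1, "Propensity score matching for APOL1 high-risk and APOL1 low-risk with eGFR>60 cohort". It has 851 high-risk participants, and 944 low-risk participants of whom 874 are matched.
- **Model selection.** SAP 6.4.2 searches about 1 million protein combinations. SAP 6.4.3 then takes the model with the lowest deviance in the testing set, and adds: "This finalized model was refitted on the entire training dataset to derive the final coefficients".
- **Evaluation.** SAP 7 describes a general function that computes its metrics on a test set. It does not say which high-risk participants supply the cross-genotype result.

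**The concern.** The two sides of the comparison differ in genotype, and also in whether the score was built on them. Matching on age, sex, eGFR, UACR and comorbidity cannot balance the second difference. A score that works equally well in both genotypes would look better in the high-risk group through optimism alone, and that gap could be taken as specificity to APOL1 high-risk people.

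No optimism correction is planned for this contrast. The bootstrap is named for feature stability (Protocol 3.7), imputation uncertainty (SAP 5.3) and NNT intervals (SAP 6.5) only.

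**Working it through.** **1. Counts** (Supplementary Table 1, Appendices 1 to 3, SAP 3)
- Split: 680 + 171 = 851, and 680/851 = 79.9%. Since 80% of 851 is 680.8 and 80% of 1,113 is 890.4, the split is of the 851.
- Composite events: 121 + 32 = 153; 153/851 = 17.98%, as stated; 121/153 = 79.1% are training events.
- Low-risk: 944 + 51 = 995; matched 874 + 38 = 912. High-risk: 851 + 262 = 1,113.
- Training data therefore make up 680 of the 851, and none of the 995 low-risk or 262 CKD participants.
- Protocol 3.2 gives 967 African-ancestry low-risk participants, against 995 in SAP 3 and Appendix 3. That needs reconciling but does not affect this point.

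**2. The two possible readings of the high-risk side**
- *All 851*, as in Appendix 1: about four fifths of the people and events were used to choose proteins and fit coefficients.
- *The 171*, as SAP 7 suggests: these people did not fit the coefficients, but under SAP 6.4.3 their outcomes helped choose the model.

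In both cases the low-risk participants played no part.

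**3. Direction, by simulation with the same outcome model in both genotypes (true difference zero)**

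*Simulation A* (Cox model, Harrell's C, 40 runs per setting). Nine proteins were chosen in 680 people from 1,510 candidates (20% of 7,549), plus four clinical covariates. Assumed protein correlation was 0.3. For protein log hazard ratios per SD of 0, 0.10, 0.15, 0.20 and 0.30, C in the 851 minus C in 874 unseen people was 0.106, 0.055, 0.058, 0.057 and 0.043. With the nine proteins fixed in advance (60 runs; log hazard ratios 0.1, 0.2, 0.3) the gap was 0.021, 0.007 and 0.011.

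*Simulation B* (binary outcome, linear fit, AUC, 15 runs per setting). There were 7,549 independent proteins, one clinical score and the 680/171 split. Nine proteins were either ranked in training only, or taken as the best of 500 random nine-protein sets judged on the 171.

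| True signal | Selection | AUC, 171 | AUC, 851 | AUC, low-risk | 851 minus low-risk | 171 minus low-risk |
|---|---|---|---|---|---|---|
| None | training only | 0.501 | 0.721 | 0.499 | 0.222 | 0.002 |
| None | on the 171 | 0.675 | 0.658 | 0.499 | 0.159 | 0.175 |
| Clinical | training only | 0.638 | 0.791 | 0.626 | 0.165 | 0.012 |
| Clinical | on the 171 | 0.776 | 0.748 | 0.677 | 0.072 | 0.099 |
| Clinical + 9 proteins | training only | 0.665 | 0.794 | 0.663 | 0.132 | 0.002 |
| Clinical + 9 proteins | on the 171 | 0.745 | 0.725 | 0.638 | 0.088 | 0.107 |

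Gaps are means of unrounded differences. The 171 agree with the low-risk group only when they had no part in selection.

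**4. Precision if only the 171 are used** (Hanley-McNeil, ignoring censoring)

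SE² = [A(1−A) + (m−1)(Q₁−A²) + (n−1)(Q₂−A²)]/(mn), with Q₁ = A/(2−A), Q₂ = 2A²/(1+A), m events and n non-events.
- Assumed A = 0.80: Q₁ = 0.6667, Q₂ = 0.7111.
- 171 (m = 32, n = 139): SE 0.0493, half-width 1.96 × 0.0493 = 0.097. Over A from 0.70 to 0.85 it runs from 0.109 to 0.087.
- 851 (m = 153, n = 698): SE 0.0224, half-width 0.044.
- 874 low-risk (m = 135, n = 739): SE 0.0237.
- Difference, 171 vs 874: 1.96 × √(0.0493² + 0.0237²) = 0.107. Difference, 851 vs 874: 0.064.

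**The case against.** The strongest reply is that Appendix 1 is a balance table. It holds baseline data, event counts and follow-up, but no APRS result. The only section on performance works on a test set, and its code uses training outcomes only for the censoring distribution. A reader might infer from Appendix 1 that high-risk performance is computed in all 851; the documents do not say so. The captions of Supplementary Figures 2 and 3, which show AUC by subgroup for each genotype, give no numbers. That part of the reply stands: the gap is an unnamed analysis set, not a documented choice of the 851.

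It does not clear the plan, because SAP 6.4.3 as written uses the testing set for selection. If that wording is a slip for validation folds inside the training set, the 171 would be clean, but the SAP would have to say so.

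Two further replies have weight. The plan gives no rule for judging specificity and does not list genotype specificity among the Protocol 2 objectives, so reading it as a high-risk minus low-risk gap in discrimination is an inference from SAP 3. And ARIC and UK Biobank already offer contrasts unseen in both arms, though the plan does not make them the basis for judging specificity.

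A reader might also extend the point to the 262 CKD participants as evidence on genotype. They are APOL1 high-risk themselves. Optimism would flatter the preserved-eGFR group against them, but that is not a genotype contrast, and composite event rates differ widely (17.98% vs 55.34%).

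**Conclusion.** The concern holds in this form: the high-risk set for the cross-genotype APRS comparison is not named, and both sets the plan points to are optimistic while the low-risk set is not. Part of any high-risk advantage in discrimination could therefore be optimism.

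The counts are exact. The bias favours the high-risk side whenever selection or fitting used those participants. Its size is not established. The gaps for the 851 (0.04 to 0.11 in Simulation A, 0.07 to 0.22 in Simulation B) and for a test set used in selection (0.10 to 0.18) depend on assumed signal, protein correlation and simplified searches. Neither simulation reproduces the planned elastic-net search, the number of runs is small, and no Monte Carlo error is available. They should not be read as estimates of bias in this study, nor as showing that a true genotype difference is absent.

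**What to change.** - In SAP 3 and 7, name the high-risk set for every cross-genotype or CKD comparison.
- Use cross-fitted scores for the 851, with the whole protein selection and tuning repeated inside each fold.
- Use the 171 alone only if SAP 6.4.3 is changed so that model selection takes place entirely in the training set.
- Label any other APRS result in the 851 as apparent performance.
- Make the contrasts unseen in both arms the main evidence on genotype specificity: ARIC (314 high-risk vs 2,021 African-American low-risk), supported by UK Biobank (204 high-risk of 1,171 of African descent, leaving 967). Report a confidence interval for the difference in tAUC. UK Biobank is the weaker support because some proteins are imputed from models trained on PMBB.

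The cost is SAP wording and extra computing, with no new data. The high-risk estimate will be lower and less favourable. Cross-fitting should avoid most of the precision loss shown for the 171. Precision in ARIC and UK Biobank cannot be worked out here because their event counts are not given.

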## **4 Data elements, preprocessing, and QC**

### **4.1 Clinical variables**

- Demographics: age (years), sex, genetic ancestry.
- Baseline labs: serum creatinine (to compute eGFR using CKD-EPI 2021), UACR (spot urine albumin/creatinine; log-transform for modeling), SBP/DBP, BMI, etc. For continuous labs, use the value closest to proteomic draw 2 months before or 1 month after sampling. For multiple measurements in the window, use the value nearest the draw date. Convert UACR to mg/g and log2 or natural log as specified (log2-UACR used in final model).
- Comorbidities: diabetes mellitus status, hypertension, cardiovascular disease history, etc.

### **4.2 Proteomics (SOMAScan in PMBB)**

The proteomic assays for this study were performed in two runs (batches) using identical laboratory protocols, instrumentation, reagent lots where possible, and operator procedures. Because the data were produced in two batches, we evaluated potential batch effects before modeling. The initial showed apparent separation by assay

run. Investigation revealed that samples in Run 2 had systematically higher baseline eGFR, so run was confounded with this clinical variable.

[figure not shown]

To determine whether the observed separation reflected technical batch bias or underlying biological differences, we adjusted each protein for baseline. PCA on the eGFR-adjusted residual no longer showed run-driven clustering, and formal tests of association between PC1 and PC2 and run were non-significant after adjustment. Based on these diagnostics, we concluded that the initial run separation was driven by biological differences in eGFR rather than a technical batch effect; accordingly, no additional batch-correction was applied in the derivation analyses.

[figure not shown]

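### SAP 4.2 clears assay run by testing two principal components, which leaves a run shift in the nine score proteins unexamined

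*Combined protocol and SAP*

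**What the plan says.** SAP 4.2 describes two assay runs under common procedures, with the same "reagent lots where possible". The data first separated by run, and "samples in Run 2 had systematically higher baseline eGFR, so run was confounded with this clinical variable". The remedy was that "we adjusted each protein for baseline". The sentence stops there, but the next one shows that the variable is eGFR: "PCA on the eGFR-adjusted residual no longer showed run-driven clustering". Tests of PC1 and PC2 against run were non-significant; the text gives no estimate, interval or p-value. The SAP infers that "we concluded that the initial run separation was driven by biological differences in eGFR rather than a technical batch effect", and on that basis "no additional batch-correction was applied in the derivation analyses".

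The score (Protocol 3.7) contains nine proteins plus age, sex, eGFR and log2 UACR. No run variable appears there, in SAP 6.4 and its pseudocode, or in SAP 7. The 80/20 split is stratified by outcome in Protocol 3.7 and by key clinical parameters in SAP 6.4.1. Neither names run.

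The text describes no protein-level run estimate, bridging samples or results by run. The two figures in SAP 4.2 could not be seen for this review.

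**The concern.** The diagnostic and the decision concern different things. PC1 and PC2 summarise the dominant variation across thousands of proteins, whereas the score depends on nine. A shift in a few proteins, or in a minority of them in mixed directions, hardly moves those two axes. A non-significant result would then be expected whether or not the score proteins are shifted, so it cannot justify leaving run out.

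At stake is whether the nine coefficients, and the ranking of participants from different runs, partly reflect the assay. A shift unrelated to outcome weakens a protein's true association. A shift combined with a run-outcome link beyond the covariates could add a spurious one.

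**Working it through.** The plan states no figure on this point, so there is nothing to reproduce.

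**1. Inputs.** From the documents: two runs and 7,549 proteins (SAP 4.2, Protocol 3.2), 851 participants with 153 events in the derivation set (SAP 3), and nine proteins in the score (Protocol 3.7). Not given, and therefore assumed: the share of samples in one run, q = 0.3 to 0.5; the eGFR gap between runs, d = 0.3 to 1.5 SD; and the size of any run shift.

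**2. Does adjusting for eGFR alone hide a shift?** The regression described has no run term, so its eGFR slope absorbs part of a technical shift. The fraction left in the residuals is 1 − r², where r² = q(1−q)d² / (1 + q(1−q)d²).

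| eGFR gap d | Fraction of shift left (q = 0.3 to 0.5) |
|---|---|
| 0.3 SD | 98% |
| 0.5 SD | 94–95% |
| 1.0 SD | 80–83% |
| 1.5 SD | 64–68% |

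For example, q = 0.5 and d = 1 give r² = 0.25/1.25 = 0.20, so 80% is left. Absorption is minor unless the gap is large.

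**3. Do the PC1/PC2 tests see the shift?** With two independent tests at 0.05 and no shift, at least one is significant in 1 − 0.95² = 9.75% of cases. Simulation results, with assumed structures throughout:

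- n = 851, 7,549 proteins, ten latent factors, q = 0.5, d = 1, 60 repeats each. Run was flagged in 5% with no shift, 2% with a 0.5 SD shift in nine proteins, and 5–10% with a 0.5 SD shift in 5% of proteins (same or mixed directions).
- 1,113 samples (assumed split 550/563), 3,000 proteins, r = 0.28, a 0.4 SD mixed-direction shift in 10% of proteins. Both tests were non-significant in 38 of 40 repeats (5% flagged). The shift left averaged 0.37 SD, matching 0.4 × (1 − 0.28²) = 0.37.
- Two further sets with other assumed structures and 0.4 SD shifts. Sparse mixed-direction shifts were flagged in 0% and in 10–13%. A same-direction shift in 10% of proteins was flagged in 25%, a shift in half of the proteins in 35–55%, and a shift in all proteins in 40–50% in one set and 95–100% in the other.

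The tests are thus nearly uninformative for sparse mixed-direction shifts and partly informative for broad ones.

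**4. Would a per-protein check do better?** Fit log2 protein on eGFR and run. For a shift of s SD, the expected z is s × √(851 q(1−q)(1−r²)). At a two-sided level of 0.05/9 the critical value is 2.77. With q = 0.5, d = 0.5 and s = 0.3, z = 0.3 × √(851 × 0.25 × 0.941) = 4.25, which gives 93% power. Over q = 0.3 to 0.5 and d = 0.5 to 1.0, power is 37–52% for 0.2 SD, 81–93% for 0.3 SD and over 99% for 0.5 SD. The 95% CI half-width is about 0.14 to 0.16 SD. In the first simulation, per-protein tests with 5% false discovery control found 98% of the shifted proteins when only nine were shifted.

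**5. What would a missed shift do?** With a 50:50 split, a true log hazard ratio is multiplied by 1/(1 + 0.25s²). If run has hazard ratio g given the covariates, the spurious log hazard ratio per SD is about ln(g) × 0.25s/(1 + 0.25s²).

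| Shift s | True log HR kept | Spurious HR per SD, g = 1.2 / 1.5 / 2.0 |
|---|---|---|
| 0.5 SD | 94% | 1.02 / 1.05 / 1.09 |
| 1.0 SD | 80% | 1.04 / 1.08 / 1.15 |

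**6. Would validation expose it?** A random split that ignores run puts both runs in the training and test sets, so the PMBB test set shares any artefact. ARIC used its own visit-2 assays (Protocol 3.3) and is independent of these runs. UK Biobank is only partly so: its shared proteins are mapped to SomaScan distributions and its missing proteins are imputed from models trained on PMBB data (Protocol 3.4, SAP 5.1 and 5.2).

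**The case against.** The SAP can be read narrowly: it explains the separation that was seen, and eGFR is a reasonable explanation. The word additional also leaves room for routine assay normalization. Both points stand. However, the decision to do nothing further rests on that explanation and reaches every protein, not only the leading components.

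eGFR is an unpenalized covariate, so the one documented route from run to outcome is adjusted for in the Cox model. This stands for the fitted score. It does not cover the pre-ranking by univariate AUC in SAP 6.4.2, for which no adjustment is described.

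A broad shift would often have been noticed, an artefact of these runs should not replicate in ARIC, and three of the nine proteins (WFDC2, MMP7, CILP2) have CRIC hazard ratios in the same direction (Supplementary Table 2). All of this stands and lowers the stakes.

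A reader might infer more than the documents support:

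- *That the score is biased by a batch effect.* No run difference in any score protein is reported, in either direction.
- *That the search over about 1 million combinations favours run-shifted proteins.* This needs run to predict outcome given the covariates, and no event rates by run are given. Without that link, a shift adds noise and makes a protein less attractive.
- *That the runs hold 550 and 563 samples.* Protocol 3.2 says "expanded from 550 in the prior dataset" but does not mention runs, and low-risk participants were included as well.

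**Conclusion.** The point holds as a gap in evidence. Non-significant PC1/PC2 tests on eGFR-adjusted residuals do not exclude a technical run shift in the nine score proteins, because they flag sparse mixed-direction shifts of 0.4 to 0.5 SD about as often as no shift at all. The main weakness is looking at only two components; absorption by the eGFR regression is secondary.

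The documents do not show that a shift exists. If one of 0.5 SD does, the likely effect is small: about 6% attenuation of a true log hazard ratio, or a spurious hazard ratio of 1.02 to 1.09 per SD. These sizes rest on assumed run shares, eGFR gap, shift size and run hazard ratio, none of which the documents give. The change is worth making because run membership is known and the check is cheap.

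**What to change.** - **SAP 4.2.** For each of the nine proteins, fit log2 protein on eGFR and run in the eGFR >60 set and report the run difference with its 95% CI. Add run sizes and event rates by run. Limit the conclusion to saying that eGFR explains the separation on the leading components. A non-zero difference would not by itself prove a technical cause, since the runs may differ in other characteristics.
- **SAP 6.4 and 7.** Add a refit of the final APRS Cox model stratified by run, and report discrimination within each run. A constant log2 shift cancels from the stratified partial likelihood, so centring is not needed for the coefficients. Centre the proteins for the estimated run difference when the score is computed, so that participants from the two runs can be ranked together.
- **Only if a material run difference is found,** repeat the protein selection with run-centred proteins. Rerunning the whole search by default is not justified.

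The cost is a short table and one extra refit, a small loss of precision, and possibly slightly different coefficients.
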